### Methods for additional analyses (e.g., subgroup analyses): {20b}

To quantify the participants’ engagement, we will use the graphical experiment builder in Gorilla to give participants an option to rewatch the video before ending the study. We will record a timestamp when the participant reaches the end of the second time point, the moment when they play the videos, and the moment when they end the study. Participants who skip the video or watch it for less than 3 seconds are considered as not engaging. For the participants who watch the video, we will record the length of time spent watching the videos. We will use regression models to describe the effects of sociodemographic factors and the Sodium questionnaire score with engagement time.

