### Objectives {7}

In this study, we aim toEvaluate the effect of SAS videos on knowledge about dietary sodium intake in the short- and medium-termEvaluate the effect of SAS videos on behavioral expectation to reduce sodium consumption in the short- and medium-termMeasure voluntary engagement with SAS video content

We hypothesize, that SAS videos help increase knowledge about dietary sodium intake in the short- and medium-term, but knowledge may decrease during the 2-week follow-up phase.

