### Outcomes {12}

As primary outcomes, we will measure the immediate and medium-term effects of the short, animated storytelling intervention video on knowledge about dietary sodium. Secondary outcomes are the immediate and medium-term effects of the short, animated storytelling intervention on the behavioral expectation to reduce sodium intake as well as voluntary post-trial engagement with the video content.

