### Participant timeline: {13}

Participants will be enrolled over a 4-week period on the Prolific Academic platform. Phase 1 of the trial (video viewing and subsequent knowledge testing) will occur on a rolling basis, with Phase 2 (follow-up knowledge testing) taking place 2 weeks subsequently, across all arms. After both phases have been completed, each participant will be offered post-trial access to both videos. Their voluntary view time will be recorded as a measure of participant engagement with this health education medium (Table 1).

**Table 1 Tab1:** Schedule of enrolment, interventions, and assessments

**Timepoint****	**Study period**							
	**Enrolment**	**Allocation**	**Post-allocation**					**Close-out**
	***-t***_***1***_	**0**	***Intervention video (t***_***1***_***)***	***Attention placebo video (t***_***1***_***)***	***Sodium and behavioral expectation questionnaire (t***_***1***_***)***	***2-week interval***	***Sodium and behavioral expectation questionnaire (t***_***2***_***)***	***Post-trial video access (all videos)***

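### The engagement regression names the knowledge score but not trial arm, so the score coefficient can absorb arm differences, and the engagement time itself is not fixed

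*Protocol article*

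**What the plan says.** Outcomes {12} lists "voluntary post-trial engagement with the video content" as a secondary outcome. The Secondary outcomes paragraph of {20a} describes an analysis for behavioral expectation only, so engagement is measured and modelled solely in Methods for additional analyses {20b}.

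- **Model.** "We will use regression models to describe the effects of sociodemographic factors and the Sodium questionnaire score with engagement time". Arm is not among the named regressors.
- **What is offered.** {20b} says Gorilla will "give participants an option to rewatch the video before ending the study". Participant timeline {13} says "each participant will be offered post-trial access to both videos", and Table 1 marks post-trial access to all videos for all four arms.
- **What is timed.** The stamps are the end of the second time point, "the moment when they play the videos, and the moment when they end the study". Separately: "For the participants who watch the video, we will record the length of time spent watching the videos".
- **Threshold.** "Participants who skip the video or watch it for less than 3 seconds are considered as not engaging".

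Objectives {7} hypothesises that "SAS videos help increase knowledge about dietary sodium intake in the short- and medium-term".

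**The concern.** Arm may affect both sides of this regression. It is meant to move the score. It also fixes prior exposure: at close-out the sodium video is a repeat for the Intervention Arm and new to the other three; the placebo video is a repeat for the Attention Placebo Arm and new to the others. If having seen a video changes the wish to watch it again, a regression without arm can report a link between knowledge and engagement that exists only because arms differ on both.

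The second problem is the dependent variable. The text moves between one video and two, and the listed stamps do not show when viewing stopped or which video was playing. A missing covariate can be added at analysis. A stamp that was never logged cannot be recovered.

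**Working it through.** **The plan's own figure.** None is given for the engagement analysis, so there is nothing to reproduce. The inputs are:

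- Four arms, 1:1:1:1 (Sequence generation {16a–c}), so each arm is a fraction 0.25.
- 10,000 recruited with 20% attrition (Sample size {14}): N = 10,000 × 0.8 = 8000, if every completer is analysed.
- D, the Intervention Arm's effect on the score in within-arm SD. The planning value is 0.1; 0.3 and 0.5 are assumed for range. D is taken at two weeks, the only time at which all four arms have a score. The other arms are taken as equal to each other.
- E, the drop in engagement time from having already seen a video, in within-arm SD. The protocol gives neither size nor sign. Assumed: 0.5, and 0.2 for comparison.
- No association between score and engagement within any arm.

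**Case A: engagement drops in the Intervention Arm only** (for example, sodium-video time is the outcome). The between-arm covariance is 0.25 × 0.75 × D × E = 0.1875DE, so in size

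r = 0.1875DE / √[(1 + 0.1875D²)(1 + 0.1875E²)].

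**Case B: engagement drops equally in both video arms** (for example, time on both videos is summed, so each of these arms has a repeat). The covariance is 0.25DE − 0.25D × 0.5E = 0.125DE, so

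r = 0.125DE / √[(1 + 0.1875D²)(1 + 0.25E²)].

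In both, z = r√8000 = 89.44r, and the false-association rate is the chance that a normal variable with mean z and SD 1 lies outside ±1.96. A drop gives r a negative sign; sizes are shown.

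Worked for D = 0.3, E = 0.5:
- A: 0.028125 / √(1.016875 × 1.046875) = 0.0273; z = 2.44; rate 68%.
- B: 0.01875 / √(1.016875 × 1.0625) = 0.0180; z = 1.61; rate 36%.

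| D | A: r, z, rate (E = 0.5) | B: r, z, rate (E = 0.5) | Rate at E = 0.2 (A / B) |
|---|---|---|---|
| 0.1 | 0.0092, 0.82, 13% | 0.0061, 0.54, 8% | 6% / 6% |
| 0.3 | 0.0273, 2.44, 68% | 0.0180, 1.61, 36% | 17% / 10% |
| 0.5 | 0.0448, 4.00, 98% | 0.0296, 2.65, 75% | 37% / 19% |

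**Viewers only.** If time is modelled only among those who watch, N falls. At D = 0.3, E = 0.5, Case A gives 41% if half watch (N = 4000) and 19% if one in five does (N = 1600). Both fractions are assumed.

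**With arm in the model**, this induced part of the score coefficient is zero by construction.

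**The outcome, sections side by side.** {20b} offers a second viewing of one video, then speaks of several; {13} offers two; Table 1 offers all. A second viewing is impossible for the two do-nothing arms, which saw no video at time point 1. The 3-second rule refers to one video without saying which. The videos last 3:09 (189 s) and 3:29 (209 s), 398 s together. If time were summed, 189 s could be the whole sodium video or most of the placebo video.

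**The case against.** The strongest case against rests on five points.

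- **The bias may be trivial.** At the planning effect of 0.1 SD the induced correlation is at most 0.009 for drops up to 0.5 SD. This stands, although Sample size {14} chose 0.1 as a deliberately small detectable effect, not as a forecast.
- **The arm effect on engagement is assumed**, in size and in sign. This stands. A reader might infer that the score–engagement association is confounded; the protocol supports only that it can be.
- **The timing rule is inferred.** A reader might conclude that viewing time is computed from play to study end and pooled over two videos, so that idle time counts as viewing. {20b} does not say so. It states separately that viewing length will be recorded, and gives neither a formula nor a rule for summing. What stands is that the listed stamps alone could not supply a per-video time or a stop time.
- **Sodium-video time need not be the target.** Objectives {7} and Outcomes {12} refer to storytelling video content generally, and the placebo is also an animated story. So it cannot be said that the wrong outcome is measured, only that the outcome is not pinned down.
- **The aim is descriptive, and a full covariate list may sit in an analysis plan not shown.** This lowers the weight of the omission. But {20b} does name its regressors for a secondary outcome, and the conflict over which videos are offered and timed is within this document.

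**Conclusion.** The point holds in a limited form. The stated engagement model leaves out a randomised factor that is expected to shift one of its named regressors and may well shift its outcome. The score coefficient is therefore open to arm-induced bias. With 8000 completers and an assumed 0.5 SD drop, the false-association rate is about 8–13%, 36–68% and 75–98% at score effects of 0.1, 0.3 and 0.5 SD. The lower figure applies if both video arms drop, the higher if only the Intervention Arm does. A smaller drop or a viewers-only analysis reduces all of them.

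A reader might extend this to the search for audiences likely to engage, which the abstract's Conclusion gives as the purpose. That does not follow: arm is randomised and so independent of demographics, and those coefficients are not directly confounded by it.

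Separately, and without any assumption, the definition of the engagement outcome is inconsistent between {13} and {20b} and within {20b}.

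**What to change.** 1. Include arm as a covariate in every engagement model that contains the score, or stratify those models by arm.
2. Before launch, log start and stop separately for each video.
3. State whether the outcome is time on the sodium video, the placebo video or both, and how it is derived from the stamps. Report first views apart from repeat views.
4. Reconcile Outcomes {12}, Participant timeline {13} and Methods for additional analyses {20b} on which videos are offered and timed, and replace the wording about a second viewing, which cannot apply to the do-nothing arms.

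An arm-by-score interaction, a two-part model (any engagement, then time among viewers) and a cap at video length are optional. A cap would discard repeat viewing, which Sample size {14} treats as relevant.

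The cost is a small change to the Gorilla task and one added covariate, with no extra participants or visits. Only the logging has to be settled before launch.

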### Methods in analysis to handle protocol non-adherence and any statistical methods to handle missing data {20c}

Participants in the study will have a time limit of 45 min to watch the short, animated storytelling videos and answer the questionnaires. All items of each questionnaire are designed such that all questions have to be answered before the questionnaire can be submitted. This will guarantee that there will no missing values in the datasets of participants included in the analyses. All participants who have participated and completed the first round of the study (time point 1) will be included in the study of medium-term effect (time point 2, 14 days later). If a participant, who submitted a completed survey at time point 1, fails to complete a survey at time point 2, their data will only be included in the immediate effect analysis. Participants who do not watch the videos or answer the questionnaire items at either time point will be excluded from the analysis.

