## Methods

### Trial design {8}

This study is a randomized-controlled parallel-group trial examining the effect of a short, animated storytelling video on knowledge and behavioral expectation to reduce dietary sodium intake. We will use an online academic research platform (Prolific Academic) to recruit and randomize 10,000 participants aged 18–59 years into four study groups.

In group 1 (intervention group), participants will be shown a SAS video on dietary sodium (see multimedia Appendix) and thereafter be asked to complete a questionnaire to assess knowledge on dietary sodium and behavioral expectation.

In group 2 (exposed control group), participants will be asked to complete a questionnaire to assess knowledge on dietary sodium and behavioral expectation (the same questionnaire as in group 1), however, without being exposed to the SAS video on dietary sodium before.

In group 3 (attention placebo control group), participants will be shown an attention placebo control (APC) video, unrelated to the outcomes measured in this trial, before being asked to complete the knowledge and behavioral expectation questionnaire.

Participants in group 4 (unexposed control group) will not view a video and will not be asked to complete the questionnaire.

Two weeks later, participants in all four arms will once again be asked to complete the knowledge and behavioral expectation questionnaire. Figure 1 illustrates the trial design.

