### Explanation for the choice of comparators {6b}

At time point 1, knowledge scores and behavioral expectation will be compared between three groups that will receive the questionnaires (*Intervention Arm – Do-nothing Exposed Arm – Attention Placebo Arm*). This comparison is intended to find out the immediate effect on knowledge and behavioral expectation about sodium intake by watching the intervention video. The primary comparison will be between the *Intervention Arm* and the *Do-nothing Exposed Arm.* By comparing these groups with the *Attention Placebo Arm* we will also be able to eliminate a potential generalized attention-activation effect from watching an animated short film (unrelated to sodium).

At time point 2, comparing the *Intervention Arm* with the *Do-nothing Un-exposed Arm* will allow us to detect potential medium-term effects of watching the intervention video on knowledge and behavioral expectation — participants in the *Do-nothing Un-exposed Arm* will neither have been exposed to the intervention video nor the sodium knowledge questions at time point 1. At time point 2, comparing the *Do-nothing Exposed Arm* with the *Do-nothing Un-exposed Arm* will provide information about the effect of simply asking sodium-related questions on medium-term knowledge and behavioral expectation to reduce dietary sodium.

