### Recruitment and strategies to improve adherence to interventions, promote participant retention, and complete follow-up {15, 11c, 18b}

Adequate participant enrolment to reach the target sample size will be guaranteed by Prolific Acedemic (ProA). ProA has a sufficiently large database of registered prospective trial participants.

The major strategy to improve adherence to the interventions in this trial is to offer payment to all participants. The payments will be given only after completing the whole survey (i.e., once the medium-term follow-up questionnaire is finished). If participants spend more than 45 min on any phase of the trial, they will be timed out of the experiment. This prevents participants from burdening the system with partially completed questionnaires. Throughout the study, investigators will have no access to the identity of the participants, so follow-up with individual participants is not possible. All incomplete datasets from participants who discontinue or deviate from intervention protocols will be descriptively reported.

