### Criteria for discontinuing or modifying allocated interventions {11b}

Participants may withdraw their consent to participate in the study at any time before or during the study. Data from incomplete surveys will not be used in the primary analysis, except at a meta-level to report the aggregate number of incomplete surveys.

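### The medium-term analysis set is tied to completing time point 1, when the Un-exposed Arm has no task, so week-2 comparisons with that arm are not between groups selected alike

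*Protocol article*

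**What the plan says.** The section on non-adherence and missing data {20c} sets the rule for the medium-term effect: "All participants who have participated and completed the first round of the study (time point 1) will be included in the study" of that effect, 14 days later. Someone who completes time point 1 but not time point 2 counts only in the immediate analysis. The section ends: "Participants who do not watch the videos or answer the questionnaire items at either time point will be excluded from the analysis". Criteria for discontinuing {11b} adds: "Data from incomplete surveys will not be used in the primary analysis".

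Trial design {8} gives the fourth arm nothing to do at time point 1: "Participants in group 4 (unexposed control group) will not view a video and will not be asked to complete the questionnaire". Table 1 agrees, with no time point 1 entry in the row for the Un-exposed Arm. The section on choice of comparators {6b} confirms that its participants "will neither have been exposed to the intervention video nor the sodium knowledge questions at time point 1". That section also says that comparing the Intervention Arm with the Un-exposed Arm at time point 2 "will allow us to detect potential medium-term effects of watching the intervention video on knowledge and behavioral expectation", and it uses Exposed versus Un-exposed for the effect of asking the questions. The primary-outcome analysis {20a} compares all four arms at time point 2 by t-test.

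The recruitment and retention section adds a time limit: "If participants spend more than 45 min on any phase of the trial, they will be timed out of the experiment".

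**The concern.** Medium-term knowledge is a primary outcome, and the article reads it against the Un-exposed Arm. The entry rule for that analysis was written for arms that have a first round. In the Intervention, Exposed and Attention Placebo Arms, completing phase 1 means finishing 30 knowledge items and three behavioural expectation questions, after a video of more than three minutes in two of the arms. People can quit or be timed out there. Nobody in the Un-exposed Arm can fail a task that the arm does not have.

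Randomisation makes the arms comparable at allocation. A filter applied afterwards in three arms but not the fourth can undo that. If people who abandon phase 1 would have scored lower at week 2, removing them raises the mean of the filtered arms. Part of the difference from the Un-exposed Arm would then be selection rather than an effect of the video or the questionnaire. The trial is powered for a difference of only 0.1 SD, so a small selection effect can matter.

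**Working it through.** **The rule, arm by arm**

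| Arm | Task at time point 1 | Task at time point 2 | Completion filters before the week-2 analysis |
|---|---|---|---|
| Intervention | video and questionnaire | questionnaire | 2 |
| Exposed | questionnaire | questionnaire | 2 |
| Attention Placebo | video and questionnaire | questionnaire | 2 |
| Un-exposed | none | questionnaire | 1 (0 participants qualify on the literal reading) |

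Four arms give six pairs at week 2. Three of them involve the Un-exposed Arm and set two filters against one.

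**The plan's own figure**

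Inputs from Sample size {14}: d = 0.1, one-tailed type I error 0.01, power 80%. The normal formula is n = 2(2.326 + 0.842)²/0.1² ≈ 2007.2, so 2008 per arm. The t-based solution is 2008.56, so 2009, which is the stated figure. From 2500 per arm, the stated 20% attrition leaves 2500 × 0.8 = 2000, the number used below.

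**Size of a possible bias**

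The documents give none of these three quantities, so all are assumptions:
- q: share of an arm lost in phase 1
- g: how much lower those people would score at week 2, in SD
- r: share of their counterparts in the Un-exposed Arm who are also lost, at time point 2

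The counterparts' share among Un-exposed completers is s = q(1 − r)/(1 − qr), and the bias is s × g. With r = 0 this is q × g, the maximum. With r = 1 it is zero.

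The standard error is √(2/2000) = 0.0316. The false-positive rate is 1 − Φ(2.326 − bias/0.0316).

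| q | g | r | s | bias (SD) | false-positive rate |
|---|---|---|---|---|---|
| 2% | 0.3 | 0 | 0.020 | 0.006 | 1.6% |
| 5% | 0.5 | 0 | 0.050 | 0.025 | 6.2% |
| 5% | 0.5 | 0.5 | 0.025/0.975 = 0.0256 | 0.0128 | 2.7% |
| 5% | 0.5 | 0.8 | 0.010/0.960 = 0.0104 | 0.0052 | 1.5% |
| 5% | 0.5 | 1 | 0 | 0 | 1.0% |
| 10% | 0.5 | 0 | 0.100 | 0.050 | 22.8% |
| 10% | 0.5 | 0.5 | 0.050/0.950 = 0.0526 | 0.0263 | 6.8% |

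For scale, 0.025 SD is a quarter of the target difference and 0.050 SD is half. If g is negative, the bias changes sign and would hide an effect.

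**The case against.** Four points can fairly be made for the plan.

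- **The Un-exposed Arm is filtered too.** It must complete the same questionnaire at time point 2, under the same 45-minute limit and the same requirement to answer every item, and payment comes only after the follow-up questionnaire. A reader might infer that filtered arms are set against an unfiltered one. The documents do not support that: the contrast is two filters against one.
- **The bias may be small.** Stable low motivation, which could make the score gap large, would also tend to remove the same people from the Un-exposed Arm at time point 2. A chance interruption need not recur, but gives little reason for a large gap. The Discussion expects minimal loss to follow-up. The 20% attrition allowance is not split by phase or arm. This stands, and it is why the no-overlap rows are upper limits.
- **Part of the exclusionary reading is inference.** The entry sentence says completers are included and does not say that only they are. No section states who is invited to time point 2, or that someone timed out in phase 1 is barred from it. This stands in part. The closing exclusion in {20c}, the dropping of incomplete surveys and the time-out wording together point towards exclusion, and nothing provides for the Un-exposed Arm.
- **Losses would be reported.** Criteria for discontinuing {11b} sets incomplete surveys aside "except at a meta-level to report the aggregate number of incomplete surveys", and a reader might infer that differences between arms will be hidden. The recruitment section also promises descriptive reporting of incomplete datasets, and neither passage rules out counts by arm. The absence of such counts from an article is not a fault in itself.

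The planned regression on demographic factors does not answer the point, because it cannot be relied on to remove selection on unmeasured motivation or prior knowledge.

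**Conclusion.** The concern holds as a defect in a stated rule for a primary outcome. As written, the rule either removes the Un-exposed Arm, and the medium-term contrast with it, or leaves the three week-2 comparisons with that arm between groups that were not selected alike. This conclusion needs no assumption about drop-out. The literal reading is clearly not intended, since Trial design {8} and Table 1 send all four arms to time point 2, but the text must say so.

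The size is conditional. The bias is at most about q × g and near zero if the same people would be lost from the Un-exposed Arm at time point 2. With g = 0.5 SD, 2000 per arm and a one-sided 1% test, the false-positive rate is about 6.2% (no overlap), 2.7% (half overlap) and 1% (full overlap) for q = 5%. For q = 10% it is about 22.8% (no overlap) and 6.8% (half overlap). A reader might take 22.8% as the expected error rate. The documents do not support that, because they give no drop-out share, score gap, direction or overlap.

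**What to change.** In {20c}, replace the entry sentence with wording such as: *All randomised participants in the four arms who have not withdrawn consent are invited to time point 2, whether or not they completed phase 1. The medium-term analysis set in every arm is everyone who submits the time point 2 questionnaire, analysed as randomised.*

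Then make three matching changes:
- Reword the last sentence of {20c} so that it does not exclude from the week-2 set the Un-exposed Arm or those who did not finish phase 1.
- State in the recruitment and retention section whether a phase 1 time-out ends participation or only that session, and how payment applies to someone who returns for time point 2.
- Report by arm the numbers randomised, completing time point 1 (the three arms that have it) and completing time point 2.

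The planned sample size does not change. The cost is protocol wording and matching set-up of the invitations. It is best done before enrolment, and the article gives the trial as not yet recruiting. There are two drawbacks. Some people in the week-2 set will have seen little of the video, which slightly dilutes the effect. Some who did not finish phase 1 will not return, so an imbalance may remain, and the counts by arm would help to show it.

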### Sample size {14}

We calculated the sample size needed for comparison of means between selected arms as detailed in the trial design. This was done independently for the primary and secondary outcomes based on the score of each questionnaire scale, upon which we selected the most conservative sample size for our study.

The sodium questionnaire consists of 8 questions, each comprising a different number of items. In total, the participants can score up to 30 points by correctly answering all of the items in the questions. As this is a new questionnaire, there is no prior information on the average score and its variability in the general population; thus, the effect size cannot be directly estimated. In addition, we assume that a consistent change in knowledge through watching an animated video could be achieved by watching the video not only once, but several times. As our study provides a one-time view of the video and measures the effect afterwards, we aim to measure a small change in the average score, presuming that these small changes could turn into larger ones by watching the video again. Thus, we power the trial to detect a small effect size for comparing the mean score between samples, i.e., *d*=0.1, smaller than the generally recommended threshold for detecting a small effect size [11]. We used the sample size formula for one-tailed comparison of the mean score with equal variance, a type I error of 0.01 to account for multiple comparisons, and a power of 80% to detect the changes in the mean score. This resulted in a sample size of 2009 individuals per arm. Accounting for a potential attrition rate of 20% (personal communication with ProA), this yields 2410 individuals per arm. For this study, we will recruit 10,000 participants (2500 per arm), which allows us to detect the potential changes in the intervention with a power higher than 80%.

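### The medium-term primary analysis is fixed as completers-only: time point 1 scores of non-returners are discarded, and selective loss is neither corrected for nor tested

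*Protocol article*

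**What the plan says.** The Outcomes section makes the immediate and the medium-term effect on knowledge both primary. The primary-outcome section compares all four arms at time point 2 with independent-groups t-tests, and adds multilevel regression with demographic covariates as needed.

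Section {20c} sets the rule for people who do not come back: if a participant with a completed time point 1 survey "fails to complete a survey at time point 2, their data will only be included in the immediate effect analysis". The same section explains that every item must be answered before submission and concludes: "This will guarantee that there will no missing values in the datasets of participants included in the analyses". It names no imputation, weighting or sensitivity analysis.

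Two other sentences in {20c} sit badly with the rule. One says that everyone who completed the first round enters the medium-term analysis. The other excludes those who do not watch the videos or answer the items at either time point.

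The sample size section reads: "Accounting for a potential attrition rate of 20% (personal communication with ProA". That figure is used only to raise the number recruited. Section {11b} keeps data from incomplete surveys out of the primary analysis "except at a meta-level to report the aggregate number of incomplete surveys", while the recruitment and retention section promises descriptive reporting of incomplete datasets. The objectives expect that "knowledge may decrease during the 2-week follow-up phase".

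**The concern.** Forced item response prevents gaps inside a submitted survey. It does nothing about a person who never opens the second survey, whose whole medium-term outcome is missing. For these people the protocol states a rule, so this is not a detail left to an analysis plan.

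Selective loss that differs by arm is plausible because phase 1 differs by arm: sodium video plus questions, questions only, unrelated video plus questions, or nothing. In the contrast that the comparator section uses for the medium-term effect (Intervention against Un-exposed), the first arm consists of people retained through two surveys and the second of people who completed one. Individual follow-up is ruled out, so the analysis is the only protection left.

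The trial is sized to detect a very small difference, which also makes it sensitive to small biases. Enlarging the sample restores precision but leaves bias unchanged.

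**Working it through.** **Inputs from the protocol (sample size section).** d = 0.1 with SD taken as 1; "sample size formula for one-tailed comparison of the mean score with equal variance"; one-sided alpha 0.01; power 80%; 2009 evaluable per arm; 20% attrition; 2500 recruited per arm.

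**Reproducing the plan's figure.** n = 2 × (2.326 + 0.842)² / 0.1² = 2008 per arm by the normal formula; the t-based version gives 2009, as stated. The figure after attrition matches 2009 × 1.2 = 2410.8, whereas 2009 / 0.8 = 2511. With 2500 recruited and exactly 20% lost, 2500 × 0.8 = 2000 remain and power is 79.8% (88.7% with all 2500). Power is therefore a minor matter here.

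**Bias of a completers-only mean.** In one arm:

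bias = loss fraction × (completer mean − dropout mean)

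The between-arm bias is the difference of these two quantities. If loss and gap are the same in both arms, it is 0.

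**Assumed dropout patterns (none is in the documents).** Dropout depends on the standardised time point 1 score through a logistic model, and the two scores correlate at 0.5 to 0.7. The shift at time point 2 is the time point 1 shift times that correlation.

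- *Strong selection in one arm, none in the other:* 20% loss in both, log-odds of dropout falling by 0.5 per SD. The completer–dropout gap at time point 1 is 0.481 SD, so the shift is 0.2 × 0.481 = 0.096 SD. At time point 2: 0.096 × 0.5 = 0.048 and 0.096 × 0.7 = 0.067 SD.
- *Selection in both arms, slightly unequal:* 20% loss, slopes 0.5 and 0.4. Bias 0.009 to 0.013 SD.
- *Mild selection in one arm:* 10% loss, slope 0.2. The gap is 0.199 SD, so the shift is 0.1 × 0.199 = 0.020 SD. At time point 2: 0.010 to 0.014 SD.
- *Equal loss and equal selection:* 0.

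**What this does to the test.** With 2000 per arm the standard error is √(2/2000) = 0.0316 SD. The one-sided rejection probability under no true effect is Φ(bias/0.0316 − 2.326):

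| Favourable bias (SD) | Type I error |
|---|---|
| 0 | 1.0% |
| 0.02 | 4.5% |
| 0.05 | 22.8% |

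An unfavourable bias of 0.02 SD would cut power at d = 0.1 from 79.8% to 58.1%.

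**Does the time point 1 score help?** In the strong one-arm case, regressing on it within arm brings the bias below 0.002 SD. That is so by construction, because dropout was generated from that score alone. It shows that the information is usable, not that real loss would be fully corrected.

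**The case against.** The 20% is a planning allowance. The Discussion expects minimal loss, and payment in every arm is withheld until the second survey is finished. Bias vanishes if loss is alike across arms, and no passage supports strong selection in one arm with none in the other. The choice of missing-data model is often left to an analysis plan. The time point 1 score cannot help the Intervention versus Un-exposed contrast, because the un-exposed arm has no such score. All of this stands. It limits the size of the concern and shapes the remedy, but it does not remove a stated rule that discards data already held and tests nothing.

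A reader might also infer three stronger things that the text does not support.

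- *The no-missing-values sentence is the reason for dropping non-returners.* It is worded for participants included in the analyses and follows from forced item response. The drop-out rule stands apart from it.
- *Loss by arm could not be shown.* Section {11b} speaks of an aggregate count, but the retention section promises descriptive reporting of incomplete datasets, and nothing forbids a breakdown by arm. The protocol simply does not commit to one.
- *The decay question is fixed as everyone at time point 1 against returners at time point 2.* The secondary-outcome section lists a matched t-test and mentions questionnaire means at both times, and a matched test uses the same people twice. The decay analysis is unclear rather than fixed as unpaired, although setting the immediate effect beside the medium-term effect would still mix two populations.

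**Conclusion.** The concern holds in a limited form. Section {20c} fixes a completers-only analysis for a primary outcome, sets aside time point 1 scores that three arms already hold, and names no check for selective loss. The attrition allowance protects sample size, not validity.

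The bias cannot be determined from the documents. Under the assumptions shown it runs from zero (equally selective loss), through about 0.01 SD (mild one-arm selection, 10% loss), to 0.05–0.07 SD (strong one-arm selection, 20% loss), against a design effect of 0.1 SD. Even 0.02 SD in the favourable direction would lift the one-sided error from 1% to about 4.5%. The change should be made; it does not call the design into question.

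**What to change.** Amend {20c} as follows.

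- **Contrasts among the three arms surveyed at time point 1, and their change from time point 1 to time point 2:** use all submitted time point 1 scores, either in a repeated-measures model (arm by time, unstructured covariance) or in multiple imputation within arm. Keep the completers-only t-test as a sensitivity analysis.
- **Contrasts with the Un-exposed Arm, including Intervention versus Un-exposed:** apply the same demographic adjustment in both arms and add a shift (tipping-point) sensitivity analysis. Do not correct one arm only by its time point 1 score. Where both arms are selective in the same way, that would remove a bias on one side that otherwise cancels.
- **Reporting:** give non-return by arm and, in the three surveyed arms, the time point 1 scores of returners and non-returners.
- **Decay:** state that the estimate uses the same participants at both times, or comes from the model above. A matched test describes returners only, and the text should say so.
- **Consistency:** reconcile the three inclusion sentences in {20c} so that one rule governs who enters the time point 2 analysis.

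The cost is wording and slightly more analysis, with no new data. The drawback is that a missing-at-random assumption must be stated and defended.
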